### Wait-list control group

2.13

Patients in the wait-list control (WLC) group will be followed for a 12-week waiting period; during this waiting period, WLC participants will be contacted by the research coordinator at the same frequency as the acupuncture groups and complete assessments at the same timepoints as the acupuncture groups. WLC patients will continue to receive their standard pain management and medical care as prescribed by their healthcare providers, including analgesic medications. Given the ethical implications of withholding a potentially beneficial treatment, we will offer all WLC patients the option of receiving 10 acupuncture treatments after week 12 (the time of the primary endpoint assessment). The WLC patients will be able to choose whether to receive EA or BFA. The WLC will provide a usual care comparison group so that we can understand the overall magnitude of the acupuncture intervention effects. The WLC will also increase the rigor of our study by controlling for regression to the mean, Hawthorne effect, and the natural history of pain processes in the usual care setting.

### Analytic approach

2.14

We will perform analysis according to the intention-to-treat (ITT) principle (ie, subjects will be analyzed according to the treatment group to which they were randomly allocated). The change in BPI pain intensity from baseline to Week 12 is the primary endpoint for this study. To maintain the overall type 1 error level at 5% for testing the primary endpoint between study arms, we will use a “gatekeeping” approach to manage the multiple statistical comparisons.^[68]^ We will first separately compare BFA to WLC and EA to WLC using the methods described below. If both acupuncture groups are significantly superior to WLC at significance threshold *P* < .025 (to maintain overall type 1 error at 5% for the 2 tests), we will compare BFA to EA using a noninferiority approach, calculating a 1-sided, 95% confidence interval.

For Aim 1, to compare the effects of acupuncture on patient-reported pain (primary outcome), physical functions, and comorbid symptoms (fatigue, sleep disturbance, anxiety, depression, and PTSD) at week 12, we will use linear mixed models (LMMs)^[69]^ to test differences between treatment arms in score changes from baseline to week 12, with randomization strata as covariates. Specifically, in addition to the randomization strata, the models will adjust for baseline score^[70]^ and will contain assessment time, treatment arm, and the time-by-treatment arm interaction. The interaction term will be used to test whether the treatment arms significantly differ in their changes from baseline. To determine the durability of treatment effects, we will report the change between week 12 and week 24 using ordinary least squares regression in the BFA and EA group separately. For secondary outcomes, we will use similar analytical strategies for physical functions, co-morbid symptoms (fatigue, sleep disturbance, anxiety/depression, PTSD), and quality of life. Additionally, we will use the weekly pain medication diaries to calculate average pain medication usage across the study time for each study participant to determine if acupuncture decreased the use of pain medication.

For Aim 2, to determine the interaction between outcome expectancy and type of needling delivery/stimulation (EA vs BFA) on pain reduction, we will define response to acupuncture therapy as a continuous outcome measured as percent change of the BPI pain intensity score from baseline to week 12. Similar to our approach in our previous study,^[71]^ we will then build a multiple linear regression model with percent reduction in BPI intensity as the dependent variable, and baseline expectancy and treatment group (EA or SA) as independent variables, including the expectancy and treatment group interaction term. The regression coefficient for the interaction term represents the between-group difference of percent reduction in BPI for one unit change in the expectancy score.

For Aim 3, we hypothesize that those participants with either AA in COMT (rs4680) or GG/AG in TCL1A (rs2369049) will be more likely than those without the genetic combination to respond to acupuncture treatments (EA or BFA). To ensure our findings can result in actionable information to guide clinical care, we will calculate percent pain intensity reduction between Week 12 and Baseline for each patient, and we will define a binary variable for clinical response to acupuncture as 30% pain reduction between week 12 and baseline. This binary response variable is consistent with that established by Farrar et al. to be a clinically important change in pain trials.^[31]^ We will perform rigorous quality control for the genotype data and will exclude genotypes that are missing for >15% subjects and subjects with >15% missing SNPs from subsequent analyses. We will tabulate genotype frequencies and perform tests of Hardy-Weinberg Equilibrium (HWE) separately for each race/ethnicity subgroup. To test our primary hypothesis that polymorphisms in COMT and TCL1A are associated with acupuncture response, we will develop multivariable linear regression models with the genotype for each SNP and treatment indictor (EA vs BFA) included as independent variables. A significant association will be claimed if the *P* value for the genotype variable is <0.025 (since we are testing 2 SNPs). In addition to assessing associations with binary pain response, we will also explore associations with changes in the raw scores and percent change. We will code each genotype as the count of minor alleles in all association testing.

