### Procedure

2.4

All potential participants will undergo an initial screening with a research coordinator in person or over the phone. During this initial screening, the research coordinator will communicate study goals and procedures and screen participants for eligibility. A study clinician will then review screened patients to confirm that all inclusion/exclusion criteria are met. Once eligibility is confirmed, participants will complete informed consent and undergo randomization.

Participants will complete assessments at weeks 0, 4, 10, 12, 16, and 24. These assessments will be completed electronically online using REDCap electronic data capture tools.^[29]^ To encourage adherence to the study procedures, all participants will be compensated with a $30 gift card at weeks 0, 4, 10, 12, 16, and 24 for a total of $180. Additionally, participants will receive reminders to complete study assessments.

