### Power analysis and sample size

2.15

For our Aim 1 sample size/power considerations for comparisons between EA versus WLC and BFA versus WLC, we calculated the smallest standardized effect size (ie, Cohen d) that we will be able to detect with 80% power, given our gatekeeping multiple testing strategy and sample sizes of 144 in each of the acupuncture arms and 72 in WLC. To estimate this smallest detectable effect size, we applied sample size calculations designed for LMMs in the context of RCTs with participant attrition.^[72]^ Using the “power.mmrm” function from the R package “longpower,” we applied the formulas in Lu et al^[72]^ to derive the smallest detectable effect size for the coefficient of the time-by-arm interaction term in our LMM (see Section 2.14), which we transformed to represent the standardized mean difference (ie, Cohen d) between 2 arms in changes in pain intensity from baseline to week 12. Assuming a 20% attrition rate across all arms by week 12, significance threshold of *P* < 0.025, a correlation between baseline and post-treatment assessments of 0.5, and power of 80%, we will be able to detect an effect size of ≥0.48 between either EA versus WLC or BFA versus WLC. This is a moderate effect size which is smaller than that found in our previous pilot trial^[65]^ (effect size of 0.76) and that detected by the meta-analysis conducted by Vickers et al (0.5 between acupuncture and standard care).^[17]^ Thus, our trial is adequately powered to detect such a difference.

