Although acupuncture is available at approximately 75% of academic cancer centers in the United States^[75]^ and has demonstrated relatively high levels of acceptability in cancer patients compared to the general population,^[76]^ only an estimated 1.7% to 31% of the oncology population has tried acupuncture,^[77]^ highlighting that important barriers to acupuncture remain. Contrary to EA, the BFA protocol can be learned and delivered by nonacupuncturist clinicians and is notable for its relative ease of administration and scalability. In 2013, the Department of Defense/Veterans Administration Joint Incentive Fund established the Acupuncture Training Across Clinical Settings (ATACS) initiative to develop, pilot, evaluate, and implement a national education program for VA health care providers. By 2016, ATACS had successfully trained >2,700 providers to deliver BFA; of these, approximately 110 were certified to train additional providers in BFA.^[24]^ Despite these successes, the real-world implementation of BFA has been hindered by the lack of high-quality data on the long-term effectiveness and side effects of BFA.^[25]^ Our study will address this evidence gap and provide clarity on the appropriate role of BFA in pain management. If BFA is found to be safe and effective, the implementation efforts by the VA will provide a template to overcome access barriers and increase acupuncture availability across healthcare systems.

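### Durability rests on separate within-arm OLS changes from week 12 to week 24, without week 16 or the randomised EA versus BFA comparison at week 24

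*Protocol article*

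**What the plan says.** Section 2.14 (Analytic approach) uses two methods in one paragraph. For Aim 1 it fits linear mixed models "to test differences between treatment arms in score changes from baseline to week 12", adjusted for baseline score and randomisation strata, with a time-by-arm interaction. For durability it changes method: "we will report the change between week 12 and week 24 using ordinary least squares regression in the BFA and EA group separately".

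Section 2.4 (Procedure) sets the visits: "Participants will complete assessments at weeks 0, 4, 10, 12, 16, and 24". Week 16 therefore lies inside the durability window.

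Section 2.13 lets wait-list patients choose EA or BFA after week 12. The Discussion accepts that this weakens long-term comparison with the wait list, and also says that the design allows no crossover between the two acupuncture arms. It names the "lack of high-quality data on the long-term effectiveness and side effects of BFA" as an obstacle to implementation that the study will address, and counts six months of follow-up as a strength.

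No section describes an EA versus BFA comparison at week 24. The gatekept noninferiority comparison concerns the week-12 primary endpoint.

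**The concern.** Three features of the stated durability analysis are weaker than the article's own week-12 method.

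- **No randomised contrast.** Fitting each arm alone yields two before-after changes. Section 2.13 says that the wait list is there to control for regression to the mean, the Hawthorne effect and natural history. A within-arm change after week 12 controls for none of these. The reason given for losing the wait-list comparison does not apply to EA versus BFA.
- **The quantity estimated.** A week-12 to week-24 change does not by itself show how much improvement from baseline remains. That needs the baseline-to-week-24 change, which is not specified.
- **Data left out.** OLS on a two-visit change makes no use of week 16 and, without imputation, needs both end scores.

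At stake is how well the trial can answer its long-term question about BFA.

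**Working it through.** **Inputs from the article (2.15).** Arms: "sample sizes of 144 in each of the acupuncture arms and 72 in WLC". Attrition: "Assuming a 20% attrition rate across all arms by week 12". Correlation: "a correlation between baseline and post-treatment assessments of 0.5". Power 80%, P < .025 per comparison with the wait list, noninferiority margin 0.33 change-score SD at one-sided .05, change-score SD 2 to 3 points.

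**Assumed, not in the article.** Attrition by week 24 of 25% to 40%; correlation 0.5 between weeks 12 and 24; score SD 2 or 3 points; log-odds of dropout after week 12 rising by 0.25 or 0.5 per point of week-12 pain; true week-12 to week-24 change +0.5 points.

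**1. The article's own figures.** With visits at weeks 0 and 12 and 80% retained, the mixed-model variance factor is 1/0.8 − 0.5² × (1/0.8 − 1) = 1.25 − 0.0625 = 1.1875. With two-sided .025,

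d = (2.241 + 0.842) × √1.1875 × √(1/144 + 1/72) = 3.083 × 1.0897 × 0.1443 = 0.485.

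Other choices of intermediate visits and dropout pattern give 0.479 to 0.485, so the stated 0.48 reproduces. A plain two-sample calculation on 115.2 and 57.6 completers gives 0.498. The margin also reproduces: n = 2 × [(1.645 + 0.842)/0.33]² ≈ 114 per arm, against 144 × 0.80 = 115.2. The week-12 power figure thus already counts on a model that uses partly observed patients.

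**2. Who contributes to the OLS change.** If dropout is permanent and nothing is imputed, 144 × 0.80 = 115.2 per arm at most. At an assumed 25%, 30% or 40% loss by week 24 this falls to 108, 101 or 86.

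**3. Bias when dropout depends on week-12 pain.** With equal SDs and correlation ρ, the bias of the complete-pair change is (1 − ρ) × (mean week-12 score of all patients seen at week 12 − mean week-12 score of those who stay). If patients with more pain leave, the bracket is positive. Higher BPI scores are worse, so the bias is toward apparent worsening. Simulated large-sample bias in BPI points:

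| Attrition by week 24 | SD 2, slope 0.25 | SD 2, slope 0.5 | SD 3, slope 0.25 | SD 3, slope 0.5 |
|---|---|---|---|---|
| 25% | 0.03 | 0.06 | 0.07 | 0.12 |
| 30% | 0.06 | 0.11 | 0.13 | 0.23 |
| 40% | 0.12 | 0.21 | 0.25 | 0.41 |

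A likelihood-type estimate using all observed scores had bias of at most 0.005 in every cell. The largest cell corresponds to stayers averaging 0.41/0.5 ≈ 0.8 points less week-12 pain than all patients seen at week 12.

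**4. Cases without bias.** If dropout is completely random, or depends on the week-16 score under equal correlations, neither estimate was biased in simulation. The standard errors differed by about 1% to 5%.

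**5. Precision of the missing contrast.** The 95% half-width for EA minus BFA, without covariate adjustment, is 1.96 × √(2/n) SD: 0.26 with 115 per arm, 0.27 with 108, 0.28 with 101 and 0.30 with 86. With SD 2 to 3 this spans 0.258 × 2 ≈ 0.52 to 0.298 × 3 ≈ 0.89 points.

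**The case against.** The strongest reply is that this is a secondary description. The article promises to report a change and attaches no test to it. Aim 1 compares each acupuncture arm with the wait list at week 12, and nothing excludes further week-24 summaries. The baseline-to-week-12 change from the Aim 1 model, read beside the later change, also gives some idea of what is retained. Restriction to patients with both scores is nowhere written: it follows from OLS on a two-visit change, and an analysis plan that is not shown could impute.

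Much of this stands, and it limits the weight of the point. Missing-data detail alone would not be a finding in a condensed article. What remains is that the article does fix the method. The absence of a randomised contrast and of a baseline-to-week-24 estimate would remain even with complete data. Adding the two changes together may also combine estimates from different patients.

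Some stronger readings are tempting but not supported:

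- A reader might infer a breach of intention-to-treat. The article defines that principle by allocation only ("subjects will be analyzed according to the treatment group to which they were randomly allocated"), and OLS within the allocated arm meets it.
- A reader might infer that the method favours a finding of sustained benefit. When patients with more week-12 pain leave, the bias runs the other way.
- A reader might expect a non-significant change to be taken as durability. The article states no such rule.
- A reader might worry about patients who relapse and leave unseen. That could hide worsening, but a mixed model would not repair it either, so it is no argument for this change.

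**Conclusion.** The point holds as an improvement to a secondary analysis. The stated method gives two uncontrolled within-arm changes, makes no use of week 16, and omits EA versus BFA at week 24, the only randomised long-term comparison still intact. These follow from the text. The restriction to at most about 115 of 144 per arm holds if the week-12 attrition is permanent and nothing is imputed.

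The size of any bias depends on the dropout mechanism. It is roughly 0.03 to 0.4 BPI points, toward apparent worsening, if patients with more week-12 pain leave, and zero if dropout is completely random. The upper end needs 40% attrition, an SD of 3 and a steep dependence on pain. A correlation above 0.5 between weeks 12 and 24 would shrink it through the factor (1 − ρ). For scale, the article's noninferiority margin is 0.67 to 1 point. The primary week-12 endpoint and its gatekeeping are unaffected.

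**What to change.** Replace the durability sentence in 2.14 with an extension of the Aim 1 linear mixed model to weeks 16 and 24 for EA and BFA, excluding wait-list data after week 12. Report:

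- for each arm, the adjusted changes from baseline to week 24 and from week 12 to week 24, with confidence intervals;
- the EA minus BFA difference at week 24, with a confidence interval.

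Label this a secondary analysis outside the gatekeeping procedure, and fit it separately so that the primary week-12 estimate does not change. The cost is a few lines of wording. The visits are already scheduled and the model family is already in the plan, so it needs no extra patients or data.

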### Inclusion and exclusion criteria

2.3

English-speaking adult patients with a primary diagnosis of any cancer type will be eligible for the study. Patients with history of metastatic cancer are eligible if they have no current evidence of disease. Active treatment with surgery, chemotherapy, and/or radiotherapy must have been completed at least 1 month before study initiation; however, patients may continue to receive hormonal treatment or maintenance targeted therapies during the study.

To be eligible, patients must also report chronic musculoskeletal pain as the primary source of pain, defined as regional (eg, joints, extremities, back) or generalized (eg, fibromyalgia, diffuse body pain). This pain must be present for at least 3 months and for at least 15 days in the preceding 30 days. Their worst pain intensity in the preceding week must be rated as ≥4 on a 0 to 10 numerical rating scale. Nonmusculoskeletal pain syndromes (eg, headache, chest pain, visceral abdominal pain) may be present as co-morbid conditions if the patient reports musculoskeletal pain as the primary source of pain.

Patients will be excluded if they have inflammatory arthritis requiring disease-modifying drugs; phantom limb pain; a pending pain-related Veteran Administration, social security, or worker's compensation disability claim by self-report; or an implanted electronically charged medical device.

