As part of our gatekeeping multiple testing procedure, we split our overall type I error rate of 5% evenly between the test of EA versus WLC and the test of BFA versus WLC. If neither, or only one of, EA or BFA is better than WLC at the *P* < .025 threshold, then there is no need for us to evaluate whether BFA is noninferior to EA. On the contrary, if both EA and BFA have significant improvements in pain intensity compared to WLC at the *P* < .025 threshold, then we will proceed to evaluate whether BFA is noninferior to EA. In this gatekeeping scenario, the alphas from both of the comparisons with WLC will propogate to our noninferiority comparison and our overall type I error rate for testing our primary endpoint will be preserved at 5%. Given our sample size, we will have 80% power to find BFA non-inferior to EA with respect to change in BPI pain intensity within a margin of .33 change-score standard deviations (SDs), assuming a 1-sided significance threshold of *P* < .05. We expect this SD to be between 2 and 3, so this margin translates to between 0.67- and 1-point difference in BPI pain intensity reduction. If we are able to demonstrate this, the interpretation would be that BFA is as good as EA with the caveat that we cannot exclude the possibility that EA is slightly better but not to the degree of clinical importance.

Aim 2 hypothesizes that there is a significant interaction between treatment and baseline AES on percent pain intensity reduction. Our preliminary data demonstrate that the regression coefficient for the interaction term between treatment and AES is 8.31 (standard error = 4.21) using percent change in BPI-severity as the dependent variable in a linear regression model including treatment, baseline AES, and their interaction.^[71]^ Using a conservative estimate of correlation (0.2) between the interaction term and the dependent variable, we need a total of 191 subjects to detect this observed interaction effect with 80% power. Thus, our proposed sample size (288 subjects in both EA and BFA groups) is sufficient to detect this observed interaction effect.

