The results of our study will need to be considered in the context of several limitations. First, although the study includes diverse cancer types across various stages and is conducted at multiple sites throughout New York and New Jersey, this is a single-center trial at a tertiary cancer center; thus, the results may not be generalizable to other populations. Second, this study does not include a sham acupuncture control group, thus precluding evaluation of the specific efficacy of these interventions; however, previous research has demonstrated that acupuncture produces significantly greater pain reduction than sham controls.^[17,18]^ Third, due to ethical concerns about withholding potentially beneficial treatments from patients with moderate-severe pain, this study allows patients in the WLC to receive acupuncture treatments after the primary endpoint; although this may limit comparison of long-term effects between the acupuncture versus WLC groups, a meta-analysis of 17,922 patients with chronic nonmalignant pain previously showed approximately 90% of the pain-relieving effects of acupuncture were sustained at 12 months relative to controls.^[78]^ Finally, our study design does not allow for crossover between the two acupuncture groups; thus, we will not be able to evaluate whether nonresponders to one acupuncture modality may demonstrate greater improvements with the other modality.

Despite these limitations, this study represents the largest RCT to date to evaluate the comparative effectiveness of two acupuncture techniques (EA and BFA) versus usual care for chronic pain in a diverse cancer population, presenting a unique opportunity to advance nonpharmacological pain management in the era of the opioid epidemic. Our investigation of clinical predictors of acupuncture response (ie, patient expectations, genetic biomarkers) will also help to inform more personalized approaches to treatment. Other strengths of our study include large sample size, rigorous design, 6-month follow-up, and inclusion of diverse cancer types across multiple stages of disease. This research has the potential to shift pain management from a one-size-fits-all paradigm towards a personalized model that integrates individuals’ expectations and genetic biomarkers to deliver “precision” acupuncture with maximal benefit to cancer survivors suffering from chronic pain.

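### The Aim 2 model omits baseline pain and the randomisation strata and mislabels an arm; prespecify a baseline-adjusted week-12 model beside percent change, because which one has more power depends on the effect scale

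*Protocol article*

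**What the plan says.** In the protocol article, Analytic approach (2.14), Aim 2 concerns "the interaction between outcome expectancy and type of needling delivery/stimulation (EA vs BFA) on pain reduction". The outcome is fixed there, since the plan is to "build a multiple linear regression model with percent reduction in BPI intensity as the dependent variable", taken over the interval up to week 12. So are the regressors: "baseline expectancy and treatment group (EA or SA) as independent variables, including the expectancy and treatment group interaction term". Neither baseline pain nor the randomisation strata appear in that list. The Aim 1 model in the same section adjusts for both.

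The label SA is defined nowhere in the article. If it stands for sham acupuncture, the Discussion states that "this study does not include a sham acupuncture control group".

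On entry pain, Inclusion and exclusion criteria (2.3) says: "Their worst pain intensity in the preceding week must be rated as ≥4". No lower limit is set for the pain intensity score that serves as the divisor.

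Power analysis and sample size (2.15) derives 191 subjects from a correlation of 0.2 at 80% power and concludes that "our proposed sample size (288 subjects in both EA and BFA groups) is sufficient to detect this observed interaction effect".

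**The concern.** Percent reduction divides by the baseline score. It cannot exceed 100% but has a long tail on the other side. The same two-point worsening counts as 100 × (1 − 3)/1 = −200% from a baseline of 1, and as 100 × (8 − 10)/8 = −25% from a baseline of 8. If expectancy acts by a similar number of BPI points whatever the starting pain, patients with low baselines carry most of the noise and power is lost. An interaction test in a secondary aim can ill afford that.

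Leaving out baseline pain and the strata gives up covariates that the trial collects anyway and that Aim 1 already uses. The wrong arm label sits in the sentence that defines the model.

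**Working it through.** **1. The plan's own figure.** Inputs from section 2.15: correlation 0.2, power 80%. A two-sided 5% level is assumed, since none is stated for Aim 2. For a 1-df partial F test, f² = 0.2²/(1 − 0.2²) = 0.04/0.96 = 0.0417. The noncentral F distribution gives n = 191 with power 80.1%, which matches the article exactly.

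**2. After attrition.** Section 2.15 assumes 20% attrition by week 12, so 288 × 0.8 = 230.4, or about 230. At the same f² the power is 86.9% (93.2% if all 288 were analysed). Since 230 exceeds 191, the conclusion stands.

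**3. Why the scale matters.** Let B be the baseline score, Y the week-12 score, and P = 100(1 − Y/B) the percent reduction.
- If Y has an additive interaction effect δ and constant residual SD σ, then on the percent scale the effect is 100δ/B and the residual SD is 100σ/B. Both grow as B falls, and P is heteroscedastic and skewed.
- If instead P has constant effect and variance, Y is the heteroscedastic one.
- On the additive scale, the baseline-adjusted score has residual variance (1 + ρ)/2 times that of the raw change. With the article's ρ = 0.5 this is 0.75.

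**4. Simulation.** 230 patients in two equal arms; baseline limited to 1–10 and week 12 to 0–10, in quarter-point steps; ρ = 0.5 in the additive model; 4,000 replicates per row. The article gives no baseline distribution, so means, SDs and effect sizes are assumptions.

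| Effect of expectancy | Baseline mean, SD | Between-arm difference per SD of AES | Percent change | Percent change + baseline | Week-12 score + baseline |
|---|---|---|---|---|---|
| Additive | 5, 2 | 0.75 points | 72.9% | 76.0% | 89.2% |
| Additive | 5, 2.5 | 0.95 points | 67.2% | 72.8% | 89.1% |
| Additive | 6, 1.5 | 0.57 points | 81.8% | 85.5% | 89.8% |
| Proportional | 5, 2 | 13 percentage points | 78.2% | 78.1% | 72.4% |

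Percent change therefore differs from the week-12 model by −16.3, −21.9, −8.0 and +5.8 points. Adding baseline to the percent model changes its power by +3.1, +5.6, +3.7 and −0.1 points.

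The skew of percent change is −2.1, −2.6 and −0.9 in the additive rows and −0.1 in the proportional row. The SD of change in the four rows is 2.0, 2.4, 1.5 and 1.9, against the 2 to 3 expected in section 2.15.

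A separate simulation, also with 230 patients and assumed baselines, gave under additive effects 66–95% for percent change, 71–96% with baseline added and 86–98% for the week-12 model. Under proportional effects percent change was about 1–5 points better, and adding baseline cost essentially nothing.

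**5. Type I error.** With no interaction, at baseline mean 5 and SD 2 (8,000 replicates), rejection rates for the three models in table order were 5.2%, 5.2% and 5.0% (additive) and 4.9%, 5.0% and 5.1% (proportional). A smaller run of 1,500 replicates per setting ranged from about 4.7% to 6.5% for percent change.

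**The case against.** Percent reduction is a deliberate and consistent choice. Section 2.15 states the Aim 2 hypothesis in percent, the preliminary coefficient of 8.31 (standard error 4.21) is on that scale, and both the responder definition and Aim 3 use percent reduction. If the effect is proportional to baseline pain, percent change is the better outcome. No figure in the article decides between the two scales. This stands, and it is why the week-12 model cannot be called more powerful without a condition.

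The simulated powers are also not forecasts for this trial. The planned correlation of 0.2 is defined on percent change, and at that effect 230 patients give 87%. The simulations only compare the models with each other.

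Several stronger readings are tempting but unsupported:
- **The percent-change test is invalid.** Type I error stays near 5%.
- **The model cannot be fitted because of SA.** The same paragraph and section 2.15 make EA versus BFA clear.
- **The outcome is undefined at a zero baseline.** Primary outcome (2.6) describes four intensity questions. If the score averages them and worst pain is still at least 4 at baseline, it cannot fall below 4/4 = 1.
- **Aim 2 is underpowered after attrition.** About 230 still exceeds 191.
- **The preliminary interaction came from a sham comparison.** The label suggests this, but the article does not say so.

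An article may leave covariate detail to a fuller document. Here, however, it spells out the regressors for Aim 2, and they differ from those for Aim 1.

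**Conclusion.** The point holds in a limited form. The Aim 2 model as written omits baseline pain and the randomisation strata, unlike Aim 1, and names an arm that the trial does not have.

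If expectancy effects are additive in BPI points, the scale of the Aim 1 model, percent change is left-skewed and gives up roughly 3 to 22 points of power against a baseline-adjusted week-12 score. If effects are proportional to baseline, it is about 1 to 6 points better. These sizes rest on assumed baseline distributions and effects. The strata were not simulated, so no gain is claimed for them in numbers. Adding baseline to the percent model helps modestly in the additive case and costs essentially nothing in the other. Neither the validity of the test nor the stated sample size is in question.

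**What to change.** In section 2.14, Aim 2:
- Replace SA with BFA.
- Add baseline BPI intensity and the two randomisation strata (accrual site and baseline opioid use) to the model.
- Prespecify a second model beside percent change: week-12 BPI intensity on baseline BPI intensity, strata, AES, arm (EA vs BFA) and AES-by-arm. State in advance which of the two is the main analysis and which the sensitivity analysis.

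The cost is wording, with no new data. The week-12 coefficient reads in BPI points rather than percent. If that model becomes the main analysis, the Aim 2 hypothesis and the effect-size basis in section 2.15 must be restated on the point scale. If it is a sensitivity analysis, section 2.15 can stay as it is.
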